## Discussion

To the best of our knowledge, this will be the first study to compare the transferability of aquatic-based and land-based reactive balance exercises on a different reactive balance task in older adults. More specifically, this study will quantify the effectiveness of a single bout intervention in water and on land on reactive balance performances, closely associated with fall prevention strategies in real-life settings, and how much it can be retained after termination of the training.

Although multifactorial exercise is the recommended form of intervention for preventing falls in older adults [42], reactive balance in specific circumstances cannot be pretermitted in exercise-based interventions. When the body loses balance, reactive balance, which is mostly exhibited in the form of reactive stepping or reach-to-grasp action, is the last line of defense to prevent a fall regardless of the cause of falls [24]. However, motor skills trained in a specific context can be transferred to an untrained task only to a limited degree. Considering the variety of mechanical postural perturbations in real-life contexts, in regards to the direction, magnitude, or point of application of the force, further studies are required to potentially corroborate and expand our results to different types of postural perturbations that commonly cause falls in older adults’ daily life.

Older adults, without regard to any clinical conditions, are always exposed to risks of falls, that are attributable to age-related neuromuscular degenerations. Thus, given the potential fall risk factors especially related to physical environments during reactive balance exercises in a dry-land condition, understanding and developing effective exercise-based interventions in a safer environment (i.e., aquatic environment) is paramount to engaging older adults in advanced balance training and ultimately prevent falls and improve their quality of life. Recently discovered evidence from a meta-analysis has suggested that aquatic exercises may be used as an effective, safer alternative to conventional land-based exercises in the elderly [15]. The results of this study may have implications for exercise prescriptions aimed at aging individuals who aspire to participate in physical activities to improve balance and prevent falls but have fear of falling or kinesiophobia.

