## Abstract

Reactive balance, a critical automatic movement pattern in response to a perturbation, is directly linked to fall prevention in older adults. Various exercise interventions have been broadly performed to improve reactive balance and thus prevent falls. Curiously, aquatic exercises have been suggested as an effective balance intervention and a safer alternative to exercises on dry land yet the efficacy of aquatic exercises on reactive balance has not been formally investigated. The present clinical trial aims to identify if skills acquired during aquatic exercise are more effectively transferred to a reactive balance task than land exercise. This study is designed as a double-blinded, randomized controlled clinical trial. Forty-four older adults aged 65 years or above who meet the eligibility criteria will be recruited and randomized into an aquatic exercise group or land exercise group. Each group will participate in the same single bout intervention that includes a ball throwing and catching task. A modified lean-and-release test will be implemented on land immediately before, after, and one week after the single bout intervention. The outcomes will include reaction time, rapid response accuracy, and mini-BESTest scores obtained from stepping and grasping reactions. All statistical analyses will be conducted using an intention-to-treat approach. Our conceptual hypothesis is that participants in the aquatic exercise group will demonstrate more improved outcome scores in the lean-and-release test when compared to those in the land exercise group. The results of the present study are expected to provide evidence to support the benefits of aquatic exercises for improving reactive balance in older adults. Further, participants may find aquatic exercises safer and more motivating, thus encouraging them to participate in further aquatic exercise programs.

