## Introduction

### Background

In daily life, reactive balance control strategies are required in response to a variety of postural perturbations, such as slips, trips, or bumps (pushes or pulls), to avoid potential falls while sitting, standing, or walking. According to WHO Global Report on Falls Prevention in Older Age, risk factors associated with physical environments (e.g., slippery surfaces, unmarked obstacles, and uneven sidewalks) play the most significant role in falls in older adults [1]. Reactive balance, which can be defined as an ability to recover a stable postural balance in response to a mechanical perturbation, requires the rapid generation of postural muscles in the trunk, lower, or upper limbs to induce proper reactions, such as swaying around the ankle or hip joints, taking a reactive step, or reaching to grasp a handhold [2]. Delayed and inappropriate generation of corrective forces from the postural muscles may result in falling and injuries [3]. Reactive balance control is supported by visual, vestibular, or somatosensory feedback, and it can be improved by repeated exposure to perturbations not only in healthy young and older adults, but individuals with neurological diseases, such as multiple sclerosis [4].

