### Randomization and allocation concealment

An experimenter, a certified athletic trainer, will screen according to the aforementioned eligibility criteria using a pre-screening medical history questionnaire and PAR-Q. Following the baseline screening, all participants meeting the eligibility criteria will be randomly assigned to either AE or LE group. Simple randomization will be applied using Random Allocation Software [33]. The numbers associated with the allocation sequence and identities will be kept in sealed envelopes and concealed until completion. Randomization and allocation will be implemented by an independent researcher not involved in any part of the study.

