### Intervention

The AE will be executed in a climate-controlled aquatic research laboratory, and the LE will be performed in a motion analysis laboratory. During AE, participants will stand barefoot on an adjustable floor of an aquatic treadmill (HydroWorx 2000TM, Middletown, PA), and the water depth will be adjusted to each participant’s xiphoid process level. Participants will sit on a chair for five minutes before AE for environmental acclimatization.

Participants will engage in a single bout intervention consisting of 120 repetitions of a ball throwing and catching task using a volleyball (Wilson Sporting Goods Co., Chicago, IL, USA). This single-session approach was selected based on a previous study, reporting the long-lasting effects of a single bout intervention with an intense reactive balance exercise [34]. Several previous studies also demonstrated that reactive balance in response to a postural perturbation has been improved after a single bout intervention [8,9,11–13].

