
### Outcome measurement

A modified lean-and-release technique devised by Bolton and Mansour (2020) will be implemented on land to assess reactive balance immediately before (pre), after (post), and one week after (follow-up) the single bout intervention [25]. Lean-and-release techniques are commonly used to assess reactive balance in various older adult populations [35–37]. This modified lean-and-release technique additionally introduces cognitive factors (i.e., response inhibition and action selection), which are important in certain situations. For safety purposes, participants will wear a harness, which is secured to the ceiling to prevent them from falling in case they fail to recover balance. The participants will then stand with both feet hip-width apart on two separate, parallel force plates (type 9260AA, Kistler AG, Winterthur, Switzerland). A horizontal cable will be attached to the safety harness at the midthoracic level and the other end to the wall behind the participants by a magnet. To simulate a forward fall (trip) situation, the experimenter will instruct participants to lean forward into a support cable while keeping both feet in contact with the floor and to remain relaxed (Fig 2). This position will require dorsiflexion of the ankle, as the rest of the body remains aligned. The forward lean position for each participant, measured by the ankle joint angle, will be determined as the minimal lean angle where a change-of-support reaction (i.e., forward step) is necessary to recover balance upon cable release [38]. Then, the magnet will be deactivated to suddenly release the cable. There are two possible settings: 1) the leg block is placed in front of both legs, and a safety handle is uncovered; or 2) the leg block is removed, and the safety handle is covered. The leg block and handle cover will be controlled via computer-triggered, servo motors. The testing session will be comprised of three blocks: 1) REACH (grasping a safety handle using their right hand while maintaining both feet fixed), 2) STEP (stepping forward using any leg), and 3) RANDOM (random variations of STEP and REACH). To control vision during the third block, participants will wear liquid crystal goggles (Translucent Technologies Inc. Toronto, ON, Canada), that will be closed at the beginning of each trial and opened 400 ms before the cable is released. An experimenter will make careful note of the stepping leg used on each trial, and the participants will be free to step with either leg during testing. The timing of foot-off of the stepping foot will be recorded using the two parallel force plates. A force-sensitive resistor (B&L Engineering, Santa Ana, CA, USA) placed on the top surface of the safety handle and one large force plate in front of the two parallel force plates will be used to detect hand contact with the safety handle during REACH and foot contact during STEP, respectively. To control the predictability of the forthcoming reactions during the third block, the settings will be randomly changed between trials via the data collection program. After sufficient practice trials to familiarize the participants with the stepping and reaching actions, five trials each of the REACH and STEP will be completed, and ten actual trials of RANDOM, including five STEP and five REACH actions in random orders, will be completed. Outcome measurements at post and follow-up will include all randomized participants within the original groups regardless of any discontinuation or deviation from intervention protocols.

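### The Discussion promises the effectiveness and retention of each exercise bout, but with two exercising arms and a repeated test only the aquatic-minus-land difference in change can be interpreted

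*Protocol article*

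**What the plan says.** **Arms.** Participants are "randomized into an aquatic exercise group or land exercise group" (Abstract). Under Randomization and allocation concealment, "all participants meeting the eligibility criteria will be randomly assigned to either AE or LE group". No group takes the test without exercising.

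**Test.** The modified lean-and-release test is given to everyone before, immediately after and one week after the bout. In each session "five trials each of the REACH and STEP will be completed, and ten actual trials of RANDOM" (Outcome measurement), preceded by familiarization trials whose number is not given.

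**Premises.** Of reactive balance control, the Background says that "it can be improved by repeated exposure to perturbations not only in healthy young and older adults". The Problem statement treats specificity as central to perturbation-based balance training. The Intervention section justifies a single session by a cited study "reporting the long-lasting effects of a single bout intervention with an intense reactive balance exercise".

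**Aim.** The Abstract and the Problem statement ask whether aquatic exercise yields greater improvement than land exercise. The Sample size calculations address the difference between groups.

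**Claim.** The Discussion opens with the comparison, then states that "this study will quantify the effectiveness of a single bout intervention in water and on land on reactive balance performances", "and how much it can be retained after termination of the training".

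**Analysis.** The Statistical analysis section specifies a 2 × 3 repeated-measures ANOVA (group by time), post-hoc tests and, for nonparametric variables, a probability of superiority for paired data.

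**The concern.** By the protocol's own premises, the test can train what it measures. Each session is a series of sudden perturbations on the outcome task itself, whereas the ball exercise contains no cable release. A gain from pre to post in either arm can therefore come from the exercise, from having taken the test before, or from both. At one week the level reached can reflect retention of the exercise or of two earlier test sessions.

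The analysis leaves room to read such gains as effects of exercise. Group has only two levels, so a Tukey procedure is needed chiefly for comparisons between time points. A paired effect size describes change within persons, not aquatic against land. Nothing in the Statistical analysis section or the Discussion says that these quantities include repeated-testing effects. If both arms improve to a similar degree, the wording would permit a conclusion that both bouts work and last, which this design cannot support.

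**Working it through.** **1. Exposure to the outcome task** (counts from Outcome measurement).

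- Per session: 5 REACH + 5 STEP + 10 RANDOM = 20 scored trials.
- Before the post-test: at least 20.
- Before follow-up: 20 + 20 = at least 40.
- Whole study: 3 × 20 = 60.
- Practice trials come on top; their number is not stated.

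**2. What the design can identify.** Write the mean change from pre in arm a at time t as

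change(a, t) = E(a, t) + L(t) + F(a, t)

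Here E is the exercise effect, L is test learning common to both arms, and F is fatigue, relevant mainly at the post-test that directly follows 120 repetitions.

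- Within one arm, only the sum is observed. Adding any constant to L and subtracting it from E in both arms leaves the expected data unchanged, so E and L cannot be separated.
- The main effect of time averages the two arms and carries the same L.
- Between arms, L cancels: change(AE, t) − change(LE, t) = [E(AE, t) − E(LE, t)] + [F(AE, t) − F(LE, t)]. Any fatigue difference that remains is a consequence of the assigned exercise.
- A test-only group would estimate L. There is none.

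**3. Illustration of the consequence.** Assumptions: zero exercise effect, no fatigue, and a common learning gain g in SD units of the pre-post change score, with normal data and two-sided α = 0.05. The documents give no value for g, so a range is shown. The sizes 19 per arm and 38 in total are the evaluable numbers in Sample size calculations; this point does not depend on how they were derived.

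For a one-sample t-test on the change score with n participants:

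P(significant) = P(|T| > t(0.975, n − 1)), where T is noncentral t with n − 1 degrees of freedom and noncentrality g√n.

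For g = 0.5, the noncentrality is 0.5 × √19 = 2.18 within an arm and 0.5 × √38 = 3.08 pooled.

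| g | Within one arm, n = 19 | Both arms pooled, n = 38 | Between-arm contrast, 19 vs 19 |
|---|---|---|---|
| 0.2 | 0.131 | 0.225 | 0.051 |
| 0.3 | 0.236 | 0.437 | 0.048 |
| 0.5 | 0.541 | 0.851 | 0.048 |
| 0.8 | 0.909 | 0.998 | 0.051 |

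The last column comes from 20,000 simulated trials per row; the same simulation gave 0.223, 0.445, 0.857 and 0.998 for the pooled column. The table uses the pre-post change only, as a simple stand-in for the three-level time factor.

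Test learning alone can thus produce a significant change over time with high probability, while the comparison between arms keeps its nominal error rate.

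**The case against.** The strongest reply is that the trial is already comparative. The aim, the hypothesis and the sample size all concern aquatic against land exercise, and the ANOVA contains the group-by-time contrast. The disputed words stand in the Discussion, directly after a comparative sentence, and naming water and land may simply name the two conditions compared. Time has to be a factor in any such model. The familiarization trials and the random order in the third block are the usual guards against test learning, and the cited evidence for lasting effects concerns an intense exercise that 20 trials at a minimal lean angle may not match.

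Much of this stands. A reader might infer that repeated testing biases the randomized comparison. The documents do not support that: both arms have the same test schedule, and common learning cancels. A reader might also infer that the plan will report equal improvement as efficacy. No passage says so; the wording only leaves it open. Nor does the Discussion's remark about aquatic exercise as an alternative to land exercise help, because it reports a cited meta-analysis and is not a conclusion planned for this trial.

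What does not stand is that the comparative reading settles the matter. Stating "how much it can be retained after termination of the training" goes beyond a difference between arms, and a paired effect size supports a within-arm reading. Familiarization may reduce learning before the scored trials, but it cannot separate what remains from the exercise effect.

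**Conclusion.** The concern holds in a limited form. The randomized comparison of change between arms is valid, provided test learning is common to both. The additional claim of effectiveness in each setting, and of its retention, cannot be supported by two exercising arms that repeat the outcome task at least 20 times before post and 40 times before follow-up.

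The size of the test-learning component is unknown. It would be tempting to say that testing explains most or all of any gain, but the documents give no figure for it. Because fatigue could push the net exercise component below zero at post, the share due to testing cannot even be bounded. The probabilities in the table rest on assumed values of g and show only that the problem could matter. The defect lies in what is claimed and in how time effects may be read, and it is open to correction before results are known.

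**What to change.** - In the Discussion, replace the sentence on effectiveness and retention with the aquatic-minus-land difference in change from pre, at post and at one week.
- In Statistical analysis, state that the main effect of time, the within-arm changes and the paired effect size are descriptive, include repeated-testing effects, and will not be interpreted as efficacy or retention of either exercise, including when both arms improve equally.
- Name repeated testing as a limitation, and possible fatigue at the immediate post-test with it.

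This costs wording only: no new arm, visit, outcome or participant. The downside is a narrower claim. If the sponsor wishes to keep the within-arm claim, a test-only reference group would be needed; at the protocol's 22 per arm, that means 3 × 22 = 66 enrolled instead of 44.
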